## **METHODS AND ANALYSIS**

### **Study design:**

The study is designed as a multicenter parallel-group non-inferiority randomized controlled trial (RCT) that complies with the CONSORT guidelines (Figure 1). A patient preference arm will be available. Patient recruitment will be done at all university hospital areas of Finland (Helsinki, Kuopio, Oulu, Tampere, Turku). The study is coordinated by Helsinki University Central Hospital, Children's Hospital pediatric orthopedic unit. Trial data analysts and person performing the recruitment will be unaware of the assigned treatment.

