## **Randomization**

After agreeing to participation in the trial patients are randomized according to a computer-generated randomization list to either operative or non-operative treatment. Randomization ratio is 1:1.

Randomization is performed by the recruiting physician who is blinded to the intervention.

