### **Patient's choice arm:**

Patients who meet inclusion criteria, but refuse participation in the randomized trial are offered to choose treatment method (operative or non-operative) and continue in a prospective parallel patient preference arm that otherwise follow the same treatment and FU protocol as the RCT.

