#### **Sample size**

Based on the results of Nikolas et al (2020) and Aasheim et al (2014) we assume clinically significant difference between the groups to be 6,8 and the standard deviation of the QuickDASH score to be 10

points. With 0,05 significance level and 80% power a non-inferiority comparison would require 27 patients per group. Allowing a 20% dropout rate the required sample would be 30 patients per group.

For subgroup analysis (less than 12 years vs. 12 years and over) 30 patients per age group needs to be collected. Assuming 50-50 split in the patients between the age groups the sample size would be 60 per ORIF and non-operated equaling a total of 120 patients.

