### **Statistical analysis:**

Data will be analyzed by using the Wilcoxon rank-sum test in Python 3.8. (Python Software Foundation, Wilmington, Delaware, U.S.A). Our hypothesis is that there is no difference in outcome between non-operative versus ORIF. Level of significance is set at  $p < 0.05$ .

Both treatment groups will be internally analyzed for differences in primary outcome regarding age (less than 12 years vs. 12 years and over) at time of injury and amount of initial fracture displacement (mm). Depending on group size, patient choice arm can be merged for analysis to same RCT group.

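### As worded, the protocol lets patients who chose their own treatment be pooled into the ORIF-versus-cast comparison on an undefined size trigger and without adjustment

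*Protocol*

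**What the plan says.** The Protocol's Study design section describes a "multicenter parallel-group non-inferiority randomized controlled trial (RCT)" and adds: "A patient preference arm will be available". Under Randomization: "Randomization ratio is 1:1".

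Under Patient's choice arm, eligible patients who "refuse participation in the randomized trial are offered to choose treatment method (operative or non-operative)" then "continue in a prospective parallel patient preference arm that otherwise follow the same treatment and FU protocol as the RCT". That section treats them as a cohort alongside the trial.

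The Statistical analysis section has two paragraphs. The first names one test, the Wilcoxon rank-sum test, and a 0.05 significance level. The second describes analyses within each treatment group of the primary outcome by age (under 12 against 12 and older) and by initial displacement. Its last sentence is: "Depending on group size, patient choice arm can be merged for analysis to same RCT group".

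The sentence gives no threshold for group size, no time for the decision and no covariate adjustment. Nothing in the section reserves the primary comparison for randomised patients. The Sample size section does not mention the choice arm.

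**The concern.** Randomisation is what makes the ORIF and cast groups comparable. Patients who choose may differ between the two treatments in displacement, age, sport level and expectations. The protocol itself treats age and displacement as relevant to the primary outcome. QuickDASH is patient-reported and patients know their treatment, so expectation can also act on the score directly.

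If these patients enter the between-treatment comparison, the estimate mixes the randomised effect with a selection effect. The larger sample narrows the interval around that mixture. In a non-inferiority trial, a bias towards the tested treatment then turns into a false claim that looks precise. A rank-sum test without covariates has no means of removing it.

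This is not a detail that can simply be left to a statistical analysis plan, because the protocol expressly grants the permission.

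**Working it through.** **Inputs from the Protocol (Sample size section).** Clinically significant difference 6.8 QuickDASH points, used as the margin; SD 10; significance level 0.05; power 80%; 27 per group; dropout 20%; 60 per treatment group in all, 30 per age stratum within each.

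**Reproducing the plan's figure.** With a true difference of 0,

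n = 2 × SD² × (z₀.₉₅ + z₀.₈₀)² / margin² = 2 × 100 × (1.645 + 0.842)² / 6.8² = 26.7, so 27 per group.

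This matches the stated 27. One-sided 2.5% would give 34, so the plan is working at one-sided 5%, although it does not say so. The check below uses one-sided 5%.

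**Assumptions not in the documents.** The protocol gives neither the size of the choice arm nor any selection bias, and it does not say which treatment is tested as non-inferior. I take cast as the tested treatment and assume:

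- 48 randomised completers per arm (60 × 0.8)
- m choice patients per arm, with m = 12, 24 or 48
- a selection bias b of 2 to 5 points among choice patients, first favouring cast
- a normal approximation for the mean difference; the named test is Wilcoxon, so the figures are indicative

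**Formulas.**

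- Merged bias B = b × m / (48 + m)
- SE = 10 × √(2 / (48 + m))
- False non-inferiority when the true difference is exactly 6.8 = Φ(B/SE − 1.645)

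**Bias favouring cast (nominal 5%).**

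| m per arm | SE | B at b = 2 | False NI | B at b = 5 | False NI |
|---|---|---|---|---|---|
| 12 | 1.826 | 0.40 | 7.7% | 1.00 | 13.6% |
| 24 | 1.667 | 0.67 | 10.7% | 1.67 | 26.0% |
| 48 | 1.443 | 1.00 | 17.1% | 2.50 | 53.5% |

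Example: m = 48, b = 5 gives 2.5/1.443 − 1.645 = 0.087, and Φ(0.087) ≈ 0.535.

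**Bias against cast.** With m = 48 and b = 2 in the other direction, false non-inferiority falls to Φ(−1.00/1.443 − 1.645), about 1%. The cost moves to power. If the treatments are truly equal, the chance of showing non-inferiority is Φ((6.8 − B)/SE − 1.645):

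| m per arm | No bias | 2 points against cast | 5 points against cast |
|---|---|---|---|
| 12 | 98.1% | 96.9% | 93.7% |
| 24 | 99.3% | 97.9% | 92.4% |
| 48 | 99.9% | 99.1% | 90.9% |

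Power is always below that of an unbiased sample of the same size. At 5 points it is also below the randomised-only figure that follows, despite the added patients.

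**Randomised patients only.** Power = Φ(6.8 / (10 × √(2/n)) − 1.645).

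- Overall, n = 48 per arm: 6.8/2.041 − 1.645 = 1.69, power 95.4%.
- One age stratum, n = 24 per arm (30 × 0.8): 6.8/2.887 − 1.645 = 0.71, power 76.1%.

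The main comparison therefore does not need pooling if recruitment is met.

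**The case against.** The strongest reply concerns scope. The sentence closes the paragraph on within-treatment analyses, not the one naming the main test. Those analyses compare younger with older patients, or less with more displaced fractures, among patients given the same treatment. Neither factor is randomised, so adding choice patients there breaks no randomised contrast. The reference to group size also fits, because the sample size is driven by the age subgroups. This stands as a plausible reading, and the fix leaves room for it. It does not settle the matter, because the wording carries no such limit. ORIF against cast within an age band would be exposed in the same way as the overall comparison.

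Three stronger conclusions may be tempting, but the documents do not support them:

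- *The merged set will be the primary analysis, or will be presented as randomised.* The protocol says only that merging is possible, and elsewhere it describes the choice arm as parallel. The defect is a permission left open.
- *The size trigger itself inflates type I error.* A decision made on numbers alone does not, and the statistician is to be blinded to treatment group. If the results were in view and whichever analysis succeeded were reported, simulation gives 6.7% to 8.6% against a nominal 5%, for 12 to 96 choice patients per arm and no selection bias. That is a worst case, and nothing in the text says it would happen.
- *The choice groups will differ, in a known direction.* They may differ. The protocol gives no direction.

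It is also fair to say that the magnitude rests wholly on assumed inputs. With a small choice arm and a 2-point bias the error is about 8%, a modest excess.

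**Conclusion.** The point holds in this form: the protocol does not exclude self-selected patients from the primary comparison of ORIF with cast, and it attaches no threshold or adjustment to their inclusion. Using the permission in that comparison would give up the protection of randomisation, whichever way the bias ran.

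Under the stated assumptions, bias of 2 to 5 points favouring cast raises a nominal 5% false non-inferiority rate to about 8–14% with 12 choice patients per arm and to 17–53% with 48. Bias against cast lowers the chance of showing true non-inferiority, relative to an unbiased sample of the same size. These ranges show sensitivity and do not predict what the trial will see. That the permission reaches the primary comparison follows from the wording alone; that it was intended to do so does not.

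**What to change.** Replace the merging sentence in the Statistical analysis section with:

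> All comparisons of ORIF with non-operative treatment for the primary and secondary outcomes use randomised patients only, whatever the group sizes. The patient choice arm is analysed and reported separately. Any combined between-treatment estimate is exploratory, is adjusted for baseline age, displacement and sport level, includes a term for randomised versus choice, and is labelled non-randomised. Choice patients may be added to the within-treatment age and displacement analyses if these are labelled observational.

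The three covariates are already collected under Baseline, so no new data are needed. Expectations are not among the listed baseline items, so adjustment could not remove that source of bias; this is a further reason to keep any combined estimate exploratory.

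The cost is the option of supplementing a slow-recruiting trial with choice patients. Comparisons of the two treatments within an age stratum also stay at about 76% power (24 completers per arm, one-sided 5%). The overall comparison keeps about 95% if 60 per arm are recruited and 20% drop out.

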### **Ethics and dissemination:**

There is no common consensus for dislocated (>2mm) medial epicondyle fractures. Treatment method vary by clinic and treating surgeon. Both ORIF and long arm cast are well established treatment methods for humeral medial epicondyle fractures. We have obtained ethical approval from Helsinki University Hospital (HUS) ethical board HUS/1443/2019. A permission to conduct the trial will be obtained by each study center. A written authorization from guardian will be acquired and child will be informed about the trial. Results of the trial will be disseminated as published articles in peer-reviewed journals.

### **Time schedule:**

Last patient FU is expected by the end of 2023 and publication by the end of 2024.

## **CONCLUSION**

The goal of this study is to compare two well-established treatment methods of dislocated non-incarcerated humeral medial epicondyle fractures in 7-16 year old patients.

**Figure 1** Flow chart of the study

[figure not shown]

| Table 1                            | Data collection time points |                 |                 |                 |                 |                     |                     |
|------------------------------------|-----------------------------|-----------------|-----------------|-----------------|-----------------|---------------------|---------------------|
|                                    | Baseline                    | Treatment day 0 | 1. Checkup 1 mo | 2. Checkup 3 mo | 3. Checkup 6 mo | 4. Checkup 12months | 5. Checkup 24months |
| Diagnosis, eliqibility             | x                           |                 |                 |                 |                 |                     |                     |
| Randomisation                      | x                           |                 |                 |                 |                 |                     |                     |
| Surgery or non-operative treatment |                             | x               |                 |                 |                 |                     |                     |
| Physical examination               | x                           |                 | x               | x               | x               | x                   | x                   |
| Questionnaires                     |                             |                 | x               | x               | x               | x                   | x                   |
| Computer tomography                | x                           |                 |                 |                 |                 |                     |                     |
| Standard radiograph                | x                           |                 | x               | x               | x               | x                   | x                   |
